### Crossover

The crossover period consists of five periods (each lasting for 2 weeks) in which the 5 different frequencies are tested. After each period, a small assessment (S1-S5) is done to evaluate the stimulation effects on pain and GPE. A 2-day wash-out period, during which the stimulation is switched off, is incorporated at the beginning of the first 2-week period (S1) and at the end of each period. The purpose of a wash-out period is to objectively determine the baseline pain levels and symptoms of CRPS when they are not masked by SCS, and to minimise the carryover effects of the previous period into the next period. The small assessments (S1-S5) comprise a stimulation evaluation, a pain diary, the McGill Pain Questionnaire and the Global Perceived Effect. Stimulation evaluation requires a patient to keep a stimulation diary in which they must answers four questions; (1) the effect(s) of stimulation on pain in the CRPS effected area, (2) if they feel paresthesia and if so where do they feel it and how is the stimulation described, (3) how they would rate the ease of use of the stimulation, (4) the advantages and (5) the disadvantages per stimulation modality. A detailed overview of the crossover period is provided in Fig. 2.

During the final evaluation (S6) a decision is made by the patient regarding which stimulation modality is to be used for the subsequent 3 months at the end of these 5 periods. This decision is mainly based on pain reduction, but also on other CRPS-related symptoms and practical matters related to the stimulation. The patient continues with their stimulation of choice for another 3 months. A switch of stimulation within these 3 months is possible in certain cases.

### Programming the various frequencies

The five stimulation modalities are all programmed in such a way the maximum effect pain be obtained. Standard 40 Hz stimulation will be performed above threshold which generates paresthesia in the affected area and is in accordance with normal practice. Both 500 Hz and 1200 Hz will be above threshold stimulation and will also generate paresthesia. At the time this study protocol was postulated there were no other reports available on how best to program 500 and 1200 Hz SCS based on mechanisms of action. Thus, in absence of evidence stating the contrary, we decided to program 500 and 1200 Hz SCS like standard 40 Hz stimulation with the intention to induce paresthesia and thus being an above threshold stimulation. Placebo stimulation is performed with the IPG switched off and thus does not generate paresthesia. The rationale is to evaluate how big a part of the pain relief could be attributed to the placebo effect. Burst stimulation is performed with fixed stimulation parameters and the intensity of the stimulation will be sub-threshold and therefore is does not generate paresthesia. The fixed parameters of burst stimulation are: an overall frequency of 40 Hz per burst complex. Each burst complex delivers 5 spikes with a frequency of 500 Hz and a pulse width per spike of 1 ms and an inter-spike interval of 1 ms. The charge is balanced during the 15 ms pause between the burst complexes.

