### Aim

This study aims to compare the effects of five different SCS modalities in patients with CRPS and determine which frequency is most effective in terms of pain reduction; these frequencies are standard stimulation with 40 Hz , 500 Hz, 1200 Hz, burst and placebo stimulation.

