## Methods

### Study design

This is a prospective randomised, double-blind and placebo-controlled crossover trial. The study is a multi-centre trial including one university hospital and four regional hospitals located throughout the Netherlands. Figure 1 provides an overview of the study and Fig. 2 a detailed overview of the crossover trial.

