### Randomisation and blinding

Randomization was performed with a computer based program at the beginning of the trial and no blocks were used since this is not viable in our study design. In our study design all patients in the crossover will be subjected to all five stimulation modalities in random order, resulting in 5! (120) different orders in which the stimulation modalities can be programmed. Only 48 (the required sample size) of these 120 potential different orders are selected at random by the computer to be used.

The specific order of the programming for an individual patient is revealed to the local SCS programmer only during each of the five crossover periods. The patient is blinded for the intervention by means of a mask that cannot be seen through. The outcome assessments at the end of each 2-week period are done by means of questionnaires. The statistician who performs the analysis of the measurements and questionnaires is blinded for the allocation key for the treatments for each patient.

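### Three modes are set to be felt and two are not, so 6 of 10 comparisons, including 3 of the 4 with placebo, can be told apart by sensation, and the placebo share of relief is not identified for tonic stimulation

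*Protocol article*

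**What the plan says.** The protocol article, Study design, states: "This is a prospective randomised, double-blind and placebo-controlled crossover trial". The Aim lists the five modes: "these frequencies are standard stimulation with 40 Hz , 500 Hz, 1200 Hz, burst and placebo stimulation".

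The section Programming the various frequencies sets out what the patient will feel in each:

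- 40 Hz: "Standard 40 Hz stimulation will be performed above threshold which generates paresthesia in the affected area".
- 500 and 1200 Hz: "Both 500 Hz and 1200 Hz will be above threshold stimulation and will also generate paresthesia".
- Burst: "the intensity of the stimulation will be sub-threshold and therefore is does not generate paresthesia".
- Placebo: "Placebo stimulation is performed with the IPG switched off and thus does not generate paresthesia".

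The same section gives the purpose of the placebo period: "The rationale is to evaluate how big a part of the pain relief could be attributed to the placebo effect". It does not restrict this to burst.

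On masking, Randomisation and blinding says: "The patient is blinded for the intervention by means of a mask that cannot be seen through". The local programmer learns the order period by period, and the statistician is blinded to the key. Under Primary outcome parameters, the patient completes all questionnaires, and VAS is the main primary outcome. Under Statistical analysis, Bonferroni-adjusted pairwise comparisons of the modes follow a significant overall test, with no distinction between pairs.

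**The concern.** A mask can hide the programming session. It cannot hide whether paresthesia is present over the following two weeks. Every patient reaches the crossover after three months of paresthesia-producing 40 Hz stimulation (Follow-up measurement T1), so its absence is easy to notice. The stimulation diary (Crossover) also asks in each period whether paresthesia is felt. Blinding the statistician does not protect a pain score that the patient assigns.

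When a felt mode is compared with an unfelt one, any expectation raised by feeling the device work, or by feeling nothing, becomes part of the measured difference. A statement that tonic stimulation beats placebo, or that burst is better or worse than tonic, would then rest on self-report that is not blind to sensation. The stated purpose of the placebo period, to apportion the relief, would not be met for the tonic modes.

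**Working it through.** **Step 1: classify the modes (Programming the various frequencies).** Felt: 40, 500 and 1200 Hz. Not felt: burst and placebo.

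**Step 2: count the pairs.** Five modes give 5 × 4 / 2 = 10 pairs.

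| Type of pair | Pairs | Count |
|---|---|---|
| Felt vs unfelt | each of 40, 500, 1200 Hz vs burst and vs placebo | 3 × 2 = 6 |
| Both felt | 40–500, 40–1200, 500–1200 | 3 |
| Both unfelt | burst–placebo | 1 |

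Of the 4 comparisons with placebo, 3 (all the tonic ones) cross the line. Only burst–placebo is matched on absence of paresthesia.

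**Step 3: reproduce the planned sample size.** Inputs from Sample size calculation: f = 0.15, correlation ρ = 0.6, power 0.8, significance level 0.05, N = 48, with m = 5 modes. The noncentrality is λ = N·m·f²/(1 − ρ) = 48 × 5 × 0.0225 / 0.4 = 13.5. The MANOVA approach with 4 and N − 4 = 44 degrees of freedom gives power 0.807, and 48 is the smallest N that reaches 0.8. The stated figure reproduces and is not in dispute.

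**Step 4: what expectation shift would look like the design effect?** Suppose there is no true difference between modes, but reported pain shifts by b (in SD units) equally in the three felt modes and not at all in the two unfelt ones. The five means are (b, b, b, 0, 0). Their variance is 0.6 × 0.4 × b² = 0.24b², so f = b√0.24. Setting f = 0.15 gives b = 0.15/√0.24 = 0.306 SD. If the VAS SD is 2 to 2.5 points (an assumption; the document gives none), this is 0.306 × 2 = 0.61 to 0.306 × 2.5 = 0.77 points.

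**Step 5: how would the overall test respond?** With N = 48, ρ = 0.6 and the MANOVA approach as in step 3:

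| Shift b (SD) | f = b√0.24 | Probability of rejecting with no true difference between modes |
|---|---|---|
| 0.1 | 0.049 | 0.12 |
| 0.2 | 0.098 | 0.41 |
| 0.306 | 0.150 | 0.81 |
| 0.5 | 0.245 | 0.998 |

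The overall test decides whether pairwise tests are made, so the sensitivity reaches the primary inference. The document gives neither the size nor the direction of such a shift. Steps 4 and 5 show how sensitive the design is and do not estimate a bias.

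**The case against.** The Discussion explains that paresthesia-free burst is what allows a switched-off period to be built in. A patient who feels nothing cannot conclude that the device is off, because it may be delivering burst. The document is also open about which modes are felt and why. This stands, and it limits what can be claimed in four ways.

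- A reader might infer that six comparisons are simply unblinded. The document does not support that. Patients are not told the allocation, and an unfelt period remains ambiguous. What it supports is that felt and unfelt modes can be told apart by sensation.
- A reader might infer that the placebo period is uninformative. It is not. The response with the device off can be described against T0, and burst minus placebo is matched on absence of paresthesia. The narrower point is that the off-period response need not equal the expectation component in a mode that is felt.
- A reader might assume that the remaining four pairs are securely blind. The document never says that the three tonic modes feel alike, and the diary asks how the stimulation is described, so 40 Hz may be recognisable after three months of use. Nor does it show that burst and a switched-off rechargeable device are indistinguishable in daily use. These pairs are matched on presence or absence of paresthesia, and no more can be said.
- A reader might size the shift from one mode standing apart from four, 0.15/0.4 = 0.375 SD. That pattern does not apply here. Three modes against two needs only 0.306 SD.

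The objection does not remove the core point. The ambiguity between burst and off does nothing for a tonic-versus-unfelt comparison, and the limitations discussed (carry-over, preconditioning, attrition) do not include this one.

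**Conclusion.** The point holds in limited form. The double-blind, placebo-controlled description does not carry over to 6 of the 10 comparisons, including 3 of the 4 with placebo, because the patient who rates the outcome can tell the two modes apart by sensation. A tonic-minus-placebo difference can be calculated, but it combines the stimulation effect with any expectation raised by feeling the device, so the placebo share of relief is not identified for the tonic modes. Tonic versus burst has the same problem.

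The count rests only on the document's own statement of which modes generate paresthesia. The size, about 0.31 SD or 0.61–0.77 VAS points to match f = 0.15, is an illustration. It assumes an equal shift in the three felt modes, none in the two unfelt, and a VAS SD of 2–2.5. No bias of that size is shown to exist.

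**What to change.** 1. State the blinding by contrast. Allocation is not disclosed to the patient, but the felt modes (40, 500, 1200 Hz) and the unfelt modes (burst, placebo) can be told apart by sensation. Do not assert that the three tonic modes are indistinguishable from each other.
2. Let only burst minus placebo support a placebo-controlled claim. Report tonic minus placebo and tonic versus burst as not blind to sensation and as including expectation, and limit the statement about the placebo share of relief to match.
3. Tabulate felt/not felt by mode from the paresthesia question already in the stimulation diary. If burst versus placebo is repeated without patients who felt the burst, label it a sensitivity analysis and note that it selects on a post-randomisation response and may itself be biased.

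The cost is a narrower placebo claim, some wording and one table from data already collected, plus the sensitivity analysis if it is run. Programming, sample size and the primary model do not change.

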### Follow-up measurement T2

The T2 assessment is performed when a patient has completed the 3-month period with the frequency of choice. This T2 evaluation enables us to compare all the primary and secondary outcomes parameters with the T1 assessment with standard SCS and the baseline T0 assessment prior to SCS therapy. The patient is actively asked whether they want to continue with the SCS program they have chosen, or want to switch to another one based on the crossover results.

### Trial completion

After completion of this trial the patient will continue with the chosen stimulation and a clinical follow-up is performed once a year by the physicians and nurses.

## Discussion

Data obtained from this trial will provide better insight as to whether SCS, as it is currently applied, is the best available therapy modality, or whether stimulation with a higher frequency or with burst stimulation results in better pain relief. Another result might be that these new modalities of stimulation are equally preferred by the patients. Irrespective of the outcomes, this trial will provide new insights into the mechanisms of action involved in SCS treatment and, particularly, in patients with CRPS.

For this trial, standard SCS was defined as stimulation with 40 Hz and corresponds with the normal stimulation setting used in our daily practice. The choice to select 500 Hz was based on studies reporting that blood flow and endogenous opioid release are at their maximum while applying SCS at this frequency [57, 59, 81]. The 1200 Hz stimulation was chosen because it is the maximum that can be generated with this IPG. Burst stimulation was selected because the stimulation differs significantly from tonic stimulation in terms of waveform and working mechanism. It is reported that burst SCS can effectively reduce pain in patients with neuropathic pain [17, 18, 82–84].

High-frequency SCS (HF-SCS) with 10,000 Hz is also available and multiple studies have shown its effect in pain patients and its ability to reduce pain over a longer period of time [85, 86]. Our 1.2 kHz stimulation does not approach the 10 kHz used in the latter studies, but no clinical studies are available that compare these frequencies. However, some animal studies have compared the effects of normal frequency SCS with different HF-SCS settings. Song et. al. compared conventional suprathreshold stimulation of 50 Hz with that of subthreshold HF-SCS at 500 Hz, 1 kHz and 10 kHz and concluded that the hypersensitivity after nerve lesions was reduced in all the HF-SCS groups and that the reduction was equal to that of the normal SCS group [87].

Burst stimulation is a new concept which requires a totally different programming algorithm in daily practice. The stimulation must be programmed to a sub-threshold current output level so that a patient will not experience paresthesia. This paresthesia free ‘side-effect’ can be used to incorporate a placebo element into the trial where paresthesia cannot be felt because the stimulation is switched off.

The question remains if a 2 week test period per frequency along with a 2 day wash-out to counteract the possible carryover effects of the various frequencies are enough. In clinical practice a patient can conclude whether the SCS is beneficial to him/her within a two week period during trial SCS. We choose to maintain the 2 week per period analogy in the crossover period which should provide the patient with enough time to decide if one of the test frequencies is beneficial or not. Moreover, by increasing the crossover period to 3 weeks or even longer the possibility of patient withdrawal from the study increases in case one of the test stimulations does not provide (sufficient) pain relief. This is further supported by what clinicians hear from patients that the pain returns when the stimulation is switched off. Some experience an instantaneous increase in pain while others report that it takes a few minutes or a few hours before the pain has fully returned, but never longer than 24 h. On these arguments we decided on a wash-out period of 2 days between the various stimulation modalities to be tested [88–90].

A potential pitfall in the design of the present trial that might influence the patient’s choice, is that the patients are preconditioned with standard stimulation for the first 3 months. On the other hand, if they do choose a SCS setting other than the standard one, it is a choice they make despite the odds being in favour of the standard stimulation.

Bias and in particular attrition bias is a serious problem that could affect the results of the trial. In our trial attrition bias will be handled by describing all patients that have dropped out of the trial before its completion and the reasons for dropping out/trial exit will be documented and provided in a flowchart in a separate manuscript with the results of this trial. The flowchart will adhere to the requirements of the CONSORT statement for transparent reporting of trials. Furthermore, data will be analysed using linear mixed models. Hence we can use all of the data, i.e., if a score is missing, it has no effect on other scores from that same patient.

With the results obtained from this study, that focuses solely on patients with CRPS, we aim to increase knowledge on the effects of SCS in this patient group. However, caution is advised when extrapolating these results to other neuropathic pain states because of the single-disease inclusion approach.

Patient recruitment and inclusion started in August 2011 and the trial is currently ongoing. Completion of the first part of the study (T0, T1 and crossover) is expected in early 2015. The completion of T2 and long-term data collection is expected towards the end of 2015.

## Abbreviations

SCS: Spinal cord stimulation
CRPS: Complex regional pain syndrome
RCT: Randomized Controlled trial
IASP: International association for the study of pain
IPG: Internal pulse generator
Hz: Hertz
MPQ: McGill Pain Questionnaire
GPE: Global Perceived Effect
HADS: Hospital anxiety and depression scale
PCS-DV: Pain catastrophizing scale Dutch version
ISS: Inventory for social support
TSK: Tampa scale for kinesiophobia
DASH: Disabilities of arm shoulder and hand questionnaire
TiC-P: Trimbos/iMTA questionnaire for costs associated with psychiatric Illness
PRODISQ: Productivity and disease questionnaire
e-QST: Electrical quantitative sensory testing
CPM: Conditioned pain modulation
CPT: Current perception threshold
PPT: Pain perception threshold
PTT: Pain tolerance threshold
